### Eligibility Criteria/Inclusion/Exclusion Criteria

Patients are eligible to participate in this domain if they have *S. aureus* cultured from blood regardless of susceptibility results for clindamycin, and emerging susceptibility results will not change this assignment. Phenotypic clindamycin susceptibility testing on all isolates will be performed centrally at the conclusion of the trial, and prespecified secondary analyses will be performed based on resistance classification. Tables 3 and 4 detail the platform and domain-level inclusion and exclusion criteria. *C. difficile*–associated diarrhea (any severity) is a key domain-level exclusion criterion (Table 4).

**Table 3. ciae289-T3:** Platform-Level Exclusion and Inclusion Criteria

Inclusion Criteria	Exclusion Criteria
*Staphylococcus aureus* complex grown from ≥1 blood culture Admitted to participating hospital at anticipated time of eligibility assessment (or, in patients who have died, if they were admitted to this site anytime from the time of blood culture collection until the time of eligibility assessment)	Time of anticipated platform entry is > 72 h after collection of the index blood culture Polymicrobial bacteremia, defined as >1 organism (at species level) in the index blood cultures, excluding organisms judged to be contaminants by the treating clinicians Currently treatment with a *systemic* antibacterial agent that cannot be ceased (except for allowed antibiotics listed in Table 1, those with limited absorption from the gastrointestinal tract or negligible antimicrobial activity against *S. aureus*) Known previous participation in SNAP Known positive blood culture for *S. aureus* (from the same silo: PSSA, MSSA, or MRSA) between 72 h and 180 d before the time of eligibility assessment Treating team deems that enrollment in the study is not in the patient’s best interest Treating clinician believes that death is imminent and inevitable Patient is for end-of-life care, and antibiotic treatment is considered inappropriate Age <18 y if pediatric recruitment is not approved at the recruiting site

Abbreviations: MRSA, methicillin-resistant *S. aureus*; MSSA, methicillin-susceptible *S. aureus*; PSSA, penicillin-susceptible *S. aureus*; SNAP, *Staphylococcus aureus* Network Adaptive Platform.

**Table 4. ciae289-T4:** Domain-Level Inclusion and Exclusion Criteria

Inclusion Criteria	Exclusion Criteria
Patients are eligible regardless of *Staphylococcus aureus* susceptibility testing results for clindamycin	Patients will be excluded from this domain if they have any of the following at the time of eligibility assessment: Previous type 1 hypersensitivity reaction to lincosamides Currently receipt of clindamycin (lincomycin) or linezolid that cannot be ceased or substituted for Necrotizing fasciitis Current CDAD (any severity) Current severe diarrhea from any cause (defined as grade ≥3^a^ or increase of ≥7 stools/d over baseline) Known CDAD in past 3 mo, or CDAD relapse (new clinical episode of diarrhea within 3 mo of a previous diagnosis of CDAD, and thought by the treating clinician to be attributable to *Clostridioides difficile*) in the past 12 mo At the time of domain eligibility assessment, >4 h has elapsed since platform entry Treating team deems that enrollment in this domain is not in the patient’s best interest

Abbreviation: CDAD, *Clostridioides difficile*–associated diarrhea.

^a^Grade ≥3 based on Common Terminology Criteria for Adverse Events (CTCAE) (version 5).

### Data Collection

Along with data collected in the core SNAP protocol, specific data collection points are required as part of the adjunctive treatment domain. Domain-specific data collection points include administration of clindamycin (or lincomycin) on the specified days if the participant is in the adjunctive treatment arm, blood culture at day 5, prespecified adverse outcomes up to day 14 and C-reactive protein levels on day 5. Table 5 details the domain-specific data collection points.

**Table 5. ciae289-T5:** Domain-Specific Schedule of Visits and Follow-up

Platform Day	1	2–4	5	14	Acute Discharge^a^
Administer clindamycin or lincomycin (if in clindamycin group)	X	X	X	…	…
Avoid clindamycin or lincomycin (if in nonclindamycin group)	X	X	X	X	X
CRP	…	…	X	…	…
SIRS criteria	…	…	X^b^	…	…
Creatinine^c^	…	…	X	X^d^	…

Abbreviations: CRP, C-reactive protein; SIRS, systemic inflammatory response syndrome.

^a^Acute discharge defined as the end of the acute index inpatient admission.

^b^Based on the white blood cell count obtained on day 5 ±1.

^c^If creatinine is measured at platform entry as part of the core protocol.

^d^Measuring serum creatinine on day 14 ± 3 is mandated only during the total index hospital stay. If the patient has been discharged, this could still be collected as part of routine follow-up if clinically indicated, but this is not mandated by the protocol.

### End Points

The primary end point for all domains within the SNAP trial is the all-cause mortality rate at day 90 after platform entry. *C. difficile* diarrhea, as determined by a clinical laboratory in the 90 days following platform entry for participants ≥2 years of age, is one of the 15 core secondary end points. The domain-specific secondary end points for the adjunctive treatment domain have been chosen to additionally determine the clinical impact and adverse event profile of adjunctive clindamycin (Table 6). A preplanned subgroup analysis based on phenotypic and genotypic clindamycin resistance markers will occur, to inform the uncertainty of whether clindamycin susceptibility is important for the proposed adjunctive activity of clindamycin in the treatment of SAB.

**Table 6. ciae289-T6:** Domain-Specific Secondary End Points for the Adjunctive Treatment Domain

Secondary End Points
Proportion of platform participants with all-cause diarrhea any time from domain reveal to platform d 14 or acute hospital discharge, whichever occurs first a. Defined as ≥3 loose stools per day, as reported by the patient, a treating nurse or doctor, or reported in medical records Change in CRP level from platform d 1 until d 5 (±1) a. CRP at d 1 means any blood CRP measurement obtained on platform d 1 or the calendar day before platform entry; if there is >1 measurement, the value recorded is that obtained closest to the time of platform entry. Proportion of platform participants with persistent bacteremia, defined as positive blood culture on platform d 5 ± 1; if blood culture at d 2 or 3 is negative, then d 5 blood culture will be assumed to be negative Proportion of platform participants meeting ≥2 SIRS criteria simultaneously on platform d 5 a. Abnormal body temperature (<36°C or >38°C) b. Tachypnea or mechanical ventilation (respirations >20/min in adults; age dependent in children) c. Tachycardia (heart rate >90/min in adults; age dependent in children) d. Abnormal leukocyte count (based on white blood cell count obtained on d 5 ± 1) Acute kidney injury (modified KDIGO stage 1; defined as an increase in serum creatinine of ≥26.5 μmol/L from platform entry [baseline] to platform d 5 *or* an increase in serum creatinine by ≥1.5 times the level at platform entry [baseline] within 14 d of platform entry) The KDIGO guidelines for acute kidney injury (AKI) define AKI as: • Increase in serum creatinine by 0.3mg/dL (= 26.5 mmol/L) or more within 48 hours OR • Increase in serum creatinine to 1.5 times baseline or more within the last 7 days OR

Abbreviations: CRP, C-reactive protein; KDIGO, Kidney Disease: Improving Global Outcomes; SIRS, systemic inflammatory response syndrome.

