## METHODS AND ANALYSIS

### Randomization

At the time of writing, participants are randomized equally to interventions within each domain at platform entry using a web-based module. Participants’ allocation in each domain is revealed at the time that domain-specific eligibility criteria are confirmed.

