### Statistical Analysis

The primary objective for this domain is to determine whether adjunctive clindamycin is superior to no adjunctive treatment. The SNAP primary end point (90-day mortality rate) is binary and modeled using a Bernoulli distribution with a logistic link function, where the general linear function includes parameters for the effect of each intervention in each domain, silo, and subgroup, interdomain interactions between interventions, ineligibility for a domain, prognostic baseline factors, country nested in region, and (calendar) time epoch. Bayesian methods are used, with weakly informative priors, and permit complete information sharing (borrowing) between silos (MSSA/PSSA/MRSA) for the adjunctive therapy domain (further details available in the published statistical appendix) [28].

The superiority of any intervention versus the domain reference is defined for the adult subgroup based on the posterior probability of an OR of <1 for the primary end point (where an OR <1.0 indicates a decrease in mortality rate for an intervention compared with the reference). A domain-stopping decision will be recommended for superiority if, at a scheduled analysis, the posterior probability of superiority is >99%. A domain-stopping decision of futility will be declared if, at a scheduled analysis, the posterior probability of an OR <0.83 (ie, 1/1.2) for the primary end point is <1%. If the thresholds for the decision criteria are not met within the domain, at any scheduled analysis, then recruitment into the domain will continue.

Scheduled primary analyses will be performed when every cohort of 500 participants in the platform reaches the day 90 end point to evaluate the domain-specific decision criteria. When maximum platform recruitment is reached or domain-specific criteria are satisfied for superiority or futility, then Bayesian analysis and reporting of secondary core and adjunctive domain end points will occur [18]. In addition, prespecified secondary analyses of the primary end point (Table 7) will be performed for the adjunctive therapy domain. Continuous, time to event, and ordinal secondary end points will be modeled using appropriate statistical distributions, link functions, and the same general linear function as for the primary end point, is documented in the published statistical appendix [28].

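### The CRP change score is modelled with the mortality model's covariates; unless day-1 CRP is among the unlisted baseline factors, the comparison is less precise than the data allow

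*Protocol article*

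**What the plan says.** Table 6 (End Points) lists the CRP end point as "Change in CRP level from platform d 1 until d 5 (±1" day). It also defines the starting value: "CRP at d 1 means any blood CRP measurement obtained on platform d 1 or the calendar day before platform entry", and where there are several, the one nearest platform entry is taken.

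The Statistical Analysis section describes the primary model as a logistic model. Its linear function has terms for interventions by domain, silo and subgroup, interdomain interactions, domain ineligibility, and "prognostic baseline factors, country nested in region, and (calendar) time epoch". The prognostic factors are not named. For continuous, time-to-event and ordinal secondary end points, the section lets the distribution and link suit the end point, but the linear function is "the same general linear function as for the primary end point". It adds that this "is documented in the published statistical appendix", which is not at hand.

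Allocation is equal: "participants are randomized equally to interventions within each domain" (Randomization).

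**The concern.** The linear function was assembled to predict 90-day death. The article lets distribution and link change between end points but holds the linear function fixed. Read literally, no end point gets a term for its own baseline measurement. For CRP this matters because the end point is a change from a measured starting value.

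Subtracting the day-1 value imposes a slope of exactly 1 of day-5 CRP on day-1 CRP. When the true slope differs from 1, part of the day-1 variation stays in the outcome as noise. A covariate lets the data set the slope and removes that noise. At stake is the width of the interval for one secondary end point. Randomisation protects the unadjusted change score from bias, so the issue is efficiency and not validity.

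**Working it through.** **Inputs.** From the article: a change-score outcome, a defined day-1 value, 1:1 allocation, and the mortality model's linear function. Not in the article: the SDs of CRP on days 1 and 5 (s1, s5) and their correlation (rho). It gives no power or precision figure for CRP, so there is no stated figure to reproduce. I assume rho from 0.2 to 0.8 and s5/s1 from 0.5 to 1.25.

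**Step 1: general comparison.** In large randomised samples, the variance of the treatment difference is proportional to
- s1² + s5² − 2·rho·s1·s5 for the change score without a baseline covariate;
- s5²·(1 − rho²) with day-1 CRP as a covariate.

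The first minus the second is s1² − 2·rho·s1·s5 + rho²·s5² = (s1 − rho·s5)², which cannot be negative. Adjustment is therefore never less precise, and the two tie only when rho·s5 = s1.

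**Step 2: equal SDs.** The ratio of adjusted to unadjusted variance is (1 − rho²) / [2(1 − rho)] = (1 + rho)/2.

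| rho (assumed) | variance ratio | fewer participants for equal precision | SE of change score ÷ adjusted SE |
|---|---|---|---|
| 0.2 | 0.60 | 40% | 1.29 |
| 0.4 | 0.70 | 30% | 1.20 |
| 0.5 | 0.75 | 25% | 1.15 |
| 0.6 | 0.80 | 20% | 1.12 |
| 0.8 | 0.90 | 10% | 1.05 |

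**Step 3: unequal SDs.** With k = s5/s1, the ratio is k²(1 − rho²) / (1 + k² − 2·rho·k). Over rho 0.2 to 0.8:
- k = 0.5 to 0.75 (spread falls by day 5): 0.20 to 0.56.
- k = 1.25 (spread rises): 0.73 to 1.00. The tie is at rho = 0.8, where 1.25² × 0.36 = 0.5625 and 1 + 1.5625 − 2 = 0.5625.

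**Step 4: does the change score itself cost anything?** Write the adjusted change model as Y5 − Y1 = a + b·T + c·Y1. Moving Y1 across gives Y5 = a + b·T + (c + 1)·Y1, so the treatment effect b is the same. Least-squares fits to three simulated data sets of 400 agreed: −0.0994, −0.0936 and −0.1455 under both forms. The identity needs outcome and covariate on one scale with an identity link. A weakly informative prior on c should disturb it little.

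**Step 5: other covariates.** These formulas compare a change score with no adjustment against one adjusted for day-1 CRP alone. The planned model already carries prognostic factors, geography and epoch. The SDs and rho should then be read as those remaining after these terms, so the actual gain may differ from the table.

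**The case against.** The strongest reply is that the covariate list for one secondary end point belongs in the statistical appendix, which the article cites, and that the unnamed prognostic factors could include day-1 CRP. This stands to the extent that the loss is conditional: if day-1 CRP is already in the model, there is none. It does not dispose of the point, because the article makes a positive statement, that the linear function is the same as for mortality, and that statement leaves no place for an end-point-specific baseline term.

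A reader might also infer more than the article supports:
- *That baseline CRP goes unused.* It is defined with care and is the subtracted term. What is not stated is its role as a covariate.
- *That a change score is the wrong outcome.* Step 4 shows that it costs nothing once the baseline is adjusted for.
- *That skewness is ignored.* The article gives no distribution for CRP, does not fix the modelling scale, and says an appropriate distribution and link will be chosen.
- *That participants without a day-1 value are lost because domain data collection lists* "C-reactive protein levels on day 5" *only.* Table 5 covers domain-specific items collected on top of the core protocol. Its creatinine row likewise shows no day-1 mark and refers the entry value to the core protocol. A blank cell does not show that day-1 CRP is uncollected, and the article does not say how a missing value is handled.
- *That a single figure measures the loss.* The ratio runs from 0.20 to 1.00 over the assumed ranges.

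**Conclusion.** The point holds as a minor, conditional one. As the article words it, the CRP model adds no term for day-1 CRP. Unless that value is already among the unlisted prognostic factors, the comparison is less precise than it could be. With equal SDs and rho assumed between 0.2 and 0.8, adjustment brings the variance to 0.60 to 0.90 of the change-score variance. The direction follows from randomisation and large samples alone. The size depends on correlations and SDs that the article does not give and on what the other covariates already explain. Only this secondary end point is affected. The primary mortality analysis and the superiority and futility rules do not depend on it.

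**What to change.** For the CRP end point, state that day-1 CRP, as Table 6 already defines it and on the same scale as the outcome, is added as a covariate to the linear function. If the statistical appendix already does this, a sentence confirming it is enough. The change-score definition need not alter.

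The cost is wording and one extra coefficient. No new data are needed, and no participant is lost by it, since anyone with a change score has a day-1 value. The article says secondary end points are analysed once a stopping criterion or maximum recruitment is reached, and it reports recruitment in progress at 26 March 2024. On that account the term could be specified before the CRP analysis is run.

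Modelling CRP on the log scale, adding a missing-baseline indicator to a day-5 analysis, and showing the source of day-1 CRP in Table 5 are optional and separate. None is needed to resolve this point.

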### Interventions

Table 2 details the interventions and the recommended doses of clindamycin for adult and pediatric participants. Adjunctive clindamycin will be given for 5 days. The recommended clindamycin doses were 600 mg given 3 times daily intravenously in adults and 15 mg/kg per dose with a maximum dose of 600 mg 3 times daily intravenously in children. These were based on French and UK guidelines recommending up to 900 mg per dose [21, 22] (Infectious Diseases Society of America guidelines for MRSA did not recommend adjunctive clindamycin in 2011 [23], with updates currently in progress [24]) and a hollow-fiber model supporting 600 mg as an appropriate dose to inhibit exotoxin production [25, 26]. Clindamycin is the preferred agent, but if unavailable it can be replaced by lincomycin.

**Table 2. ciae289-T2:** Dosing Table for *Staphylococcus aureus* Network Adaptive Platform (SNAP) Adjunctive Domain (Clindamycin) Intervention

Adjunctive Treatment	Dose	Substitutions	Renal Impairment	Oral Alternative
None	…	Nil	…	…
Clindamycin	600 mg (10 mg/kg/dose in children), given intravenously every 8 h for 5 d^a^	Intravenous lincomycin (600 mg every 8 h)	No dosage adjustment	450 mg (10 mg/kg/dose in children), given orally every 8 h

^a^On platform days 1–5.

Administering clindamycin orally is allowed for sites and investigators who prefer oral dosing for reasons of cost, convenience, or antimicrobial stewardship. The oral dose is capped at 450 mg given 3 times daily (Table 2), as this is the maximum licensed dose in most regions and higher doses tend to have poor gastrointestinal tolerability [27]. Study investigators viewed a 5-day course as the shortest duration likely to have clinical impact while balanced against the possibility of adverse effects, particularly *Clostridioides difficile*–associated diarrhea. An initial short-course treatment strategy was also believed to balance the likelihood that any effect of adjunctive clindamycin will be achieved early in the SAB course, while potential gastrointestinal side effects were presumed to be less likely with fewer days of treatment.

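### Table 6's CRP baseline rule can select a value drawn after allocation is revealed and clindamycin has started, even when a pre-reveal value exists

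*Protocol article*

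**What the plan says.** The end point in Table 6 (Protocol article, End Points) is the change in CRP from platform day 1 to day 5, give or take one day. Two rules fix its baseline:

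- Window: "CRP at d 1 means any blood CRP measurement obtained on platform d 1 or the calendar day before platform entry".
- Choice within the window: "if there is >1 measurement, the value recorded is that obtained closest to the time of platform entry".

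Other sections set the timing of treatment against that window:

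- Randomization: "allocation in each domain is revealed at the time that domain-specific eligibility criteria are confirmed".
- Table 4 lists as a domain exclusion: "At the time of domain eligibility assessment, >4 h has elapsed since platform entry". Domain eligibility is therefore assessed no later than 4 h after entry.
- The footnote to Table 2 places clindamycin "On platform days 1–5".
- Blinding and Unblinding says that the study drugs are open label, and that investigator and participant know the allocation once it is revealed.

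**The concern.** A baseline is meant to describe the participant before the randomized comparison can act. Here the window runs through the whole of platform day 1, which is also the first day of dosing, and the choice rule looks equally forwards and backwards from entry. Two consequences follow.

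First, if clindamycin changes CRP, a baseline drawn after the first dose already contains part of that change. Subtracting it removes that part from the estimate.

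Second, a CRP ordered after reveal is ordered with the arm known. Under the rule, such a sample can displace an earlier pre-reveal value if it lies closer to entry. Which value becomes the baseline can then depend on the arm.

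Other definitions in Table 6 are anchored more tightly: diarrhea is counted from domain reveal, and the creatinine baseline is the level at platform entry. CRP has a window that crosses the start of treatment.

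**Working it through.** The article states no power, sample size or effect size for CRP, so there is no figure to reproduce. The check has three parts.

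**1. Can the rule select a post-reveal value over a pre-reveal one?** Take entry at 08:00, one CRP at 06:00 the previous day, and another at 20:00 on day 1.

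- Distance of the earlier value from entry: 26 h before. It lies on the calendar day before entry, so it is inside the window.
- Distance of the later value from entry: 12 h after. It lies on platform day 1, so it is also inside the window.
- Since 12 h < 26 h, the rule takes the later value.
- Eligibility is assessed between 08:00 and 12:00. If reveal comes at that assessment, the chosen value is 8 to 12 h after reveal.

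The later value is also chosen whenever it is the only one in the window. A value between entry and reveal is harmless, because allocation is not yet known and treatment has not started.

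**2. How much of an effect could be lost?** Let D be the true effect on day-5 CRP, q the share of clindamycin-arm baselines drawn after dosing, and f the fraction of D already present in such a baseline. The arm difference is D at day 5 and q × f × D at baseline, so the expected difference in change is

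D − q·f·D = D(1 − q·f).

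The article gives neither q nor f. Over an assumed range:

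| q | f | Loss, q × f |
|---|---|---|
| 10% | 5% | 0.5% |
| 25% | 10% | 2.5% |
| 50% | 20% | 10% |

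As a guide to f, suppose the effect builds up evenly over the 96 h from day 1 to day 5. A baseline 8 h into treatment then carries 8/96 = 8.3% of it, and one at 12 h carries 12/96 = 12.5%. With f = 12.5% and q = 25% to 50%, the loss is 3.1% to 6.3%, inside the range above.

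**3. What if the drug has no effect on CRP?** Then D = 0 and a post-dose baseline causes no bias by itself. Bias needs a difference between arms in sampling. Let q1 and q0 be the shares of post-reveal baselines with and without clindamycin, and d the average movement in CRP between a pre-reveal and a post-reveal sample. The spurious difference in change is −(q1 − q0)·d. It is zero if sampling is alike in both arms. None of these three quantities is in the article, so this part cannot be sized.

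**The case against.** The strongest reply is that the problem is rare and small. The rule already favors values near entry, and those taken before reveal are sound. The example needs a gap of 26 h before entry and of 12 h after it. If platform day 1 is a calendar day, which the article does not define, reveal at 14:00 leaves at most 10 h in which a post-reveal baseline could be drawn. The attenuation is toward the null, and the handling of continuous end points is left to the statistical appendix, which is not shown. All of this stands as a limit on size. It does not remove the flaw, because the article states the baseline rule outright. The rule is also worded as what is recorded; if that governs data capture, an earlier pre-reveal value might not reach the database, and no later model could restore it.

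A reader might go further and infer that no day-1 CRP is scheduled, so that some participants have no baseline at all. Data Collection does list "prespecified adverse outcomes up to day 14 and C-reactive protein levels on day 5", and Table 5 marks CRP on day 5 only. But that schedule is expressly additional to the core protocol, which is not shown. Creatinine also has an empty day-1 cell, although its footnote points to a core measurement at entry. The missing footnote for CRP is weak evidence, so the article does not support this inference.

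A reader might also infer that randomization no longer protects the CRP comparison. That needs sampling to differ by arm in fact. The open-label design makes this possible; nothing in the article shows that it happens.

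**Conclusion.** The point holds in limited form. As written, the rule admits a baseline drawn after reveal and after the first clindamycin dose, and can prefer it to an available pre-reveal value. Under the assumed shares and timings, any true effect on change in CRP would be attenuated by about 0.5% to 10%. A further bias from arm-dependent choice of baseline is possible but cannot be quantified.

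The reach is narrow: one domain-specific secondary end point. The 90-day mortality end point and the superiority and futility rules do not use CRP. The case for acting is that the bias is avoidable by wording alone.

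**What to change.** In Table 6, define baseline CRP as the last value obtained at or before domain reveal, within the existing window, identically in both arms. Reveal is a better anchor than the first dose because it occurs in both arms.

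Where the only value in the window is post-reveal, treat the baseline as missing in the main analysis of this end point. One way is to model day-5 CRP with baseline as a covariate and handle its missingness within the model. Adjusted for baseline, day-5 CRP and change in CRP give the same treatment contrast, so the question asked does not alter. Use the post-reveal value only in a sensitivity analysis.

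Apply the same rule to participants already enrolled: the article reports 1994 in this domain as of 26 March 2024. Sample and reveal times are needed to classify their baselines. If only the closest value was captured, an earlier one may have to be retrieved from hospital records.

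The cost is a wording change and some missing baselines, in a number that the article does not allow one to estimate. The article reports domain secondary end points only after the domain stops or platform recruitment ends, and keeps investigators blinded to aggregate domain outcomes until then. The change can be made and dated before those results are known.

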### Population

All patients with SAB at participating sites are eligible to participate in the domain, within 72 hours of the collection of the index blood culture.

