### Data Monitoring and Safety

SNAP is overseen by an independent data safety monitoring committee. This comparative effectiveness trial follows the guidelines of the International Conference on Harmonization Good Clinical Practice. All the treatments being studied are known to be safe and are approved by regulatory agencies for each SNAP site for treating *S. aureus* infections. The level of reporting of adverse events depends on the regulatory requirements in each region, but at a minimum, sites will report all serious adverse events related to the treatments being studied. Common adverse effects such as kidney or liver damage and diarrhea caused by *C. difficile* will be recorded as key secondary safety end points. The trial will also closely monitor critical data points for all participants and have a central safety team to assess all serious adverse reactions.

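### The acute kidney injury end point rests on creatinine alone with no rule for dialysis, so it can count dialysis-cycle swings as events and can miss new renal replacement

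*Protocol article*

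**What the plan says.** In the protocol article, End Points, Table 6 labels the end point a modified KDIGO stage 1 and gives two criteria joined by *or*:

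- Absolute: "defined as an increase in serum creatinine of ≥26.5 μmol/L from platform entry [baseline] to platform d 5".
- Relative: "an increase in serum creatinine by ≥1.5 times the level at platform entry [baseline] within 14 d of platform entry".

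Both use serum creatinine against the platform-entry value. There is no criterion for new renal replacement and no separate rule for participants already on dialysis. The article does not mention dialysis anywhere.

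On who enters, Population states: "All patients with SAB at participating sites are eligible to participate in the domain", subject to the 72-hour limit. Neither Table 3 (platform criteria) nor Table 4 (domain criteria) lists dialysis or renal failure as an exclusion. Table 2 has a renal-impairment column, with the entry "No dosage adjustment", so participants with renal impairment are foreseen.

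On sampling, Table 5 schedules creatinine on day 5 and day 14. Footnote c sets one condition: "If creatinine is measured at platform entry as part of the core protocol". Footnote d adds: "Measuring serum creatinine on day 14 ± 3 is mandated only during the total index hospital stay".

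On the role of the end point, Data Monitoring and Safety says that "Common adverse effects such as kidney or liver damage and diarrhea caused by" *C. difficile* are recorded as key secondary safety end points.

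**The concern.** The definition is printed with its own thresholds, baseline and time windows. Applied as written, it can misclassify two identifiable groups.

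1. **On maintenance dialysis at entry.** Creatinine falls with each session and climbs again before the next. Whether the entry-to-day-5 difference reaches 26.5 μmol/L then depends on where the two samples fall in the cycle, not on kidney injury.
2. **Starting renal replacement for new AKI.** Treatment lowers creatinine. If the value was already raised at entry, or peaked between recorded samples, neither criterion need be met, and a severe case is scored as no AKI.

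The Discussion makes possible harm from adjunctive clindamycin part of the domain's question. The first error makes a real kidney harm harder to see. The second understates how often severe kidney injury occurred.

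**Working it through.** **The plan's own threshold.** With a creatinine molar mass of 113.12 g/mol, 0.3 mg/dL = 0.3 × 10 / 113.12 × 1000 = 26.5 μmol/L. The trial's threshold is therefore reproduced in μmol/L. The KDIGO text in the same cell prints the unit as mmol/L ("Increase in serum creatinine by 0.3mg/dL (= 26.5 mmol/L) or more within 48 hours"), which is a thousandfold slip and a separate correction.

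**Relative size of the absolute criterion.** Required rise = 26.5 / entry value.

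| Entry creatinine (μmol/L) | Rise needed |
|---|---|
| 80 | 33% |
| 400 | 6.6% |
| 600 | 4.4% |
| 800 | 3.3% |

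**How often dialysis variation alone meets it.** This is an assumed model, because the article has no data on it. Creatinine rises linearly from a post-dialysis to a pre-dialysis value, kidney function is unchanged, and the entry and day-5 samples fall at independent random points of the cycle. With pre-dialysis values of 500–900 μmol/L and post/pre ratios of 0.35–0.65, the absolute criterion is met 36–46% of the time. A 1.5-fold rise is met 0–18% of the time. False events come mainly from the absolute criterion.

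**Effect on the comparison.** Assumptions: true AKI 15% in controls and a true odds ratio of 1.50 in participants not on dialysis. Treated odds = 0.15/0.85 × 1.5 = 0.2647, so treated risk = 0.2647/1.2647 = 0.2093. Let *d* be the share on dialysis at entry and *q* the probability that such a participant is falsely flagged, equal in both arms by randomisation.

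- Observed control risk = (1 − *d*) × 0.15 + *d* × *q*
- Observed treated risk = (1 − *d*) × 0.2093 + *d* × *q*
- False share of control events = *d* × *q* / observed control risk

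| *d* | *q* | Control | Treated | Observed OR | False share |
|---|---|---|---|---|---|
| 1% | 36% | 0.1521 | 0.2108 | 1.49 | 2% |
| 3% | 46% | 0.1593 | 0.2168 | 1.46 | 9% |
| 5% | 50% | 0.1675 | 0.2238 | 1.43 | 15% |
| 10% | 50% | 0.1850 | 0.2384 | 1.38 | 27% |
| 15% | 50% | 0.2025 | 0.2529 | 1.33 | 37% |

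The 50% rows lie above the modelled 36–46%, so they are the pessimistic end.

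**New renal replacement.** Suppose, as an assumption, that 1 to 1.5 percentage points of true events are lost from the control arm.

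- Same points lost in each arm: 0.14 vs 0.1993 gives OR 1.53; 0.135 vs 0.1943 gives OR 1.55. Both are further from 1.
- Loss in proportion to each arm's risk: 0.14 vs 0.1953 and 0.135 vs 0.1884 both give OR 1.49. The risk ratio stays at 0.2093/0.15 = 1.395.

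This error therefore lowers the reported frequency of severe AKI. It moves the odds ratio away from 1 or hardly at all, unless loss differs between arms in some other way.

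**The case against.** The strongest reply is that this is a condensed article. The core protocol, domain appendix and statistical appendix are not shown. They may restrict who is evaluable for AKI or record renal replacement elsewhere, and footnote c already ties creatinine to a core-protocol measurement. That uncertainty stands and shapes the fix. It does not remove the point: Table 6 prints a complete rule, nothing in the article qualifies it for dialysis, and footnote c requires only an entry creatinine.

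Second, the relative criterion is not tied to day 5. A recorded pre-dialysis value, or a later value within 14 days, can still count a newly dialysed participant. This also stands. A miss requires both criteria to fail at every recorded sample, so it is possible but not certain.

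Third, the size is driven by assumptions. At 1–3% on dialysis the dilution is slight, and the article gives no share. The renal-impairment column in Table 2 shows that reduced kidney function was foreseen, not that dialysis patients were enrolled; the argument for entry rests on the absence of an exclusion.

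Fourth, reporting of treatment-related serious adverse events and central review of serious adverse reactions give a partial backstop for severe kidney events attributed to treatment.

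A reader might infer that both errors pull the comparison towards no difference. The arithmetic above does not support that for missed new renal replacement. A reader might also infer that every dialysis participant yields a false event. That depends on when the samples are taken and on an entry creatinine having been recorded.

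**Conclusion.** The point holds as a flaw in a printed end-point definition, with limited reach. In participants on maintenance dialysis with an entry creatinine, the absolute criterion can be met without kidney injury. Under the stated assumptions a true odds ratio of 1.50 is seen as about 1.46–1.49 if few participants are on dialysis (1–3%), and about 1.33–1.43 if 5–15% are and half are flagged. The dialysis share, the flagging probability, the 15% AKI risk and the odds ratio of 1.50 are all assumed.

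Missed new renal replacement is a separate weakness. It can understate the absolute frequency of severe AKI, but the documents give no basis for saying that it biases the comparison towards no effect.

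Only a secondary safety end point is affected. The 90-day mortality analysis, the superiority and futility rules and the stated power do not use it.

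**What to change.** In Table 6, make two additions to the AKI definition:

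1. Restrict the end point to participants not on maintenance dialysis at platform entry.
2. Count new renal replacement therapy started for kidney failure by platform day 14 as an event, whatever the creatinine.

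If the core protocol or an appendix already contains these rules, Table 6 should state them or refer to them. This changes how the outcome is scored and not how participants are managed.

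The cost is about one sentence and at most two yes/no fields: maintenance dialysis at entry, and new renal replacement by day 14. The downside is a slightly smaller denominator, reduced by the share on dialysis at entry, whose creatinine changes are not a valid measure of new kidney injury.
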